# Change in Contact 7 for Low transmission site

Contact 7 at age 18 months will be the last scheduled visit for children at the low transmission site. This is because the low incidence in malaria at the site means that there is a very small chance that this study will detect a rebound effect of malaria even if present.

At the high transmission site, all children will be invited to attend the clinic at the age of approximately 24 months (**contact 8**) and finger prick blood sample will be obtained for screening for malaria using Paracheck dipsticks and also for preparation of blood slides, filter paper samples and Hb. If a child is positive dipstick test is currently febrile (Temp >37.5° C) or has a history of fever with in the past 2 days, and/or has a history of taking SP for a febrile illness during the previous week, the child will be treated with Artemether - Lumefantrine.

**4.6. Randomisation and allocation of study groups**

The unit of randomization will be an individual infant. Infants will be allocated to one of the study groups by permuted block randomization. Each study drug, including placebo, will be assigned 4 group codes; there will be 16 study groups in total in each study site and these will be colour coded. An independent statistician ([name]) will prepare the randomization scheme during the preparatory phase of the study. 233 blocks of 16 blister packs of study drugs [80 blocks (1280/16 = 80) for the high transmission area, and 153 blocks (2448/16 = 153) for the low transmission area] will be prepared and the study drug codes will be kept by the independent statistician.

- 1. **Dose schedule and administration of study drugs**

The dose schedules of the study drugs are shown in Table 7a and 7b and the drug package schemes are shown in Appendix 4 and 5.

**Table 7a. Dose schedule of study drugs for IPTi course 1 & 2**

| **Study group** | **Dose on day 1** | **Dose on day2** | **Dose on day3** |
| --- | --- | --- | --- |
| Placebo | 1 tab CD placebo$  ½ tab SP placebo | 1 tab CD placebo | 1 tab CD placebo |
| SP | 1 tab CD placebo  ½ tab SP£ | 1 tab CD placebo | 1 tab CD placebo |
| Mefloquine | 1 tab CD placebo  ½ tab Mefloquine@ | 1 tab CD placebo | 1 tab CD placebo |
| Lapdap (CD) | 1 tab Lapdap#  ½ tab SP placebo | 1 tab Lapdap | 1 tab Lapdap |

$ tablets of lactose and maize starch, looking similar in size, shape and colour to Lapdap

£ sufadoxine 500mg + pyrimethamine 25mg per tab

@ mefloquine 250mg per tab

# Chlorproguanil 15mg + dapsone 18.75mg per tab (CD/Lapdap)

**Table 7b. Dose schedule of study drugs for IPTi course 3**

| **Study group** | **Dose on day 1** | **Dose on day2** | **Dose on day3** |
| --- | --- | --- | --- |
| Placebo | 1 ½ tab CD placebo$  1 tab SP placebo | 1 ½ tab CD placebo | 1 ½ tab CD placebo |
| SP | 1 ½ tab CD placebo  1 tab SP£ | 1 ½ tab CD placebo | 1 ½ tab CD placebo |
| Mefloquine | 1 ½ tab CD placebo  1 tab Mefloquine@ | 1 ½ tab CD placebo | 1 ½ tab CD placebo |
| Lapdap (CD) | 1 ½ tab Lapdap#  1 tab SP placebo | 1 ½ tab Lapdap | 1 ½ tab Lapdap |

$ tablets of lactose and maize starch, looking similar in size, shape and colour to Lapdap

£ sufadoxine 500mg + pyrimethamine 25mg per tab

@ mefloquine 250mg per tab

# Chlorproguanil 15mg + dapsone 18.75mg per tab (CD/Lapdap)

The mean age of study infants when they receive the third course of IPTi would be 9 months and the average body weight of children at 9 months of age is 8.5 kgs for girls and 9.5 kgs for boys. Thus, it is necessary to increase the dose of antimalarial drugs for the third course of IPTI. The dose of SP and MQ will be increased to 1 tab and that of Lapdap will be increased to 1 ½ tablets per day for three days.

The tablets will be crushed and mixed with honey at the time of administration. The first dose will be administered at the EPI clinic by a designated member of the study team.

Children will be observed for 30 minutes, and a repeated dose will be given if vomiting occurs within this time period.

The drugs for day 2 and 3 will be dispensed in blister packs and the caretakers will be advised to administer the drugs at home. The level of compliance and side effects of the drug will be monitored by the compliance assessment team during home visits made on day 2 and day 3. If drugs had not been given by the caretakers, the project staff will administer the drugs with the consent of the caretaker.

Oral administration of mefloquine can induce vomiting in children suffering from clinical malaria. Administration of mefloquine in two divided doses over two days may reduce the risk of vomiting. However, a single dose regime is preferable for directly observed administration of the drug in routine programme conditions. As most of the infants attending EPI clinics will be asymptomatic, the incidence of mefloquine induced vomiting may be low. We will observe the incidence of vomiting over an initial period of three months and report this information to the Data, Safety and Monitoring Board (DSMB). If the incidence of vomiting is significant, the DSMB may recommend that the schedule of mefloquine administration should be changed to a split dose (15 mg /kg on day 1 and 10 mg/kg on day 2).

(2). At the time of the day 3 follow-up, a questionnaire will be completed which asks about the health of the infant since the time of drug administration; particular attention will be paid to the occurrence of vomiting.

(3). An adverse events reporting system will be established in each of the health centres participating in the trial. Any illness that occurs within 28 days of administration of a study drug will be documented on an adverse events form . Any severe adverse event, as defined in appendix 2, will be reported to the [name], the chair of the DSMB within 1 week of the report being received. In addition, all serious adverse events will be reported to GSK regional office (fax no. [name]) with in 1 week of becoming aware of the event using the SAE form provided by GSK. A copy of the drug codes will be provided to [name].

The study is not powered to detect differences between groups in the incidence of severe malaria. However, records will be kept of all study children admitted to Same or Korogwe hospitals with severe malaria or who require blood transfusion for anaemia.

Infant mortality in the study area remains quite high (IMR 90 per 1,000 live births) so at least 100 deaths can be anticipated in study children. Mortality will not be a trial end-point, as the sample size is not sufficient for this but, on safety grounds, all deaths will be investigated by the post-mortem questionnaire technique and reported to the DSMB.

Drugs used for IPTi must not have any suppressive effect on the immune response to EPI vaccines given concurrently. Investigation of possible interactions of this kind is being co-ordinated by a committee set up for this purpose by WHO. The possible impact of SP is being studied in a number of other IPTi with SP trials and will not be investigated in this trial. However, no other study being conducted under the auspices of the IPTi consortium is investigating the effect of mefloquine. An impact on measles vaccination is the issue of most concern. Therefore, a serum sample will be collected at the age of 9 months before administering measles vaccination and one month after the administration of the vaccine. This will also be tested for the impact of Lapdap on measles vaccination. Antibody concentrations to DPT antigens will also be measured in these samples.

- 1. **Surveillance of clinical malaria**

All study infants will be encouraged to attend the study health facilities for any illness. At these visits a health questionnaire will be completed and temperature recorded using an electronic thermometer. A finger prick blood sample will be collected for Hb and malaria parasite and for detection of molecular markers of resistance from all infants attending the study health facilities for any illness that is clinically diagnosed as malaria. At the health centres one blood slides will be examined on the same day for deciding on appropriate treatment whilst the second slide will be read in the central laboratory to provide definitive diagnosis.

Children with proven or presumptive malaria will be treated according to the MoH guidelines for managing treatment failures following first line drugs. We have opted for the second line antimalarials instead of giving SP, the first line drug recommended by the MoH, because we believe that most of the break through infections will be in the SP and placebo groups and therefore a repeat dose of SP will not be appropriate in this setting where there is a high level of SP resistance.

To ensure that IPTi with any of the study drugs does not lead to a rebound in the incidence of severe malaria or anaemia during the second year of life all infants enrolled in the study will be followed until they reach the age of 24 months. During their second year of life, all episodes of possible malaria or anaemia in infants who present to health centre in the study area will be documented.

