**5. Monitoring of the trial**

The trial will be conducted under conditions of good clinical practice (GCP), following as closely as possible the ICH guidelines. Standard operating procedures (SOPs) will be developed for all major operations. A DSMB will be established to look after the trial. Members will include an experienced clinician, a statistician and a person with local knowledge of the study area. Discussions will be held with the DSMB prior to the start of the trial to identify their requirements for adverse events reporting and these will be met. The DSMB will also be consulted about the advisability of an interim analysis, in particular for the SP group as this drug may prove to be ineffective.

At each study site, a local physician will be assigned to be the local safety monitor. He or she will have access to the codes of the study drugs. All serious adverse events will be reported to the local safety monitor by the project physician. In the event of a serious adverse event associated with a study drug, the local safety monitor will be empowered to break the code for that child and, if it is considered necessary to temporarily suspend the trial, prior to discussion with the DSMB.

It is proposed that a clinical monitor will be appointed by the IPTi consortium to monitor all the trials conducted under its auspices and it is anticipated that the monitor will visit the study site on at least one occasion during the trial and provide advice that will help to ensure that the study is conducted to the highest clinical standard.

1. **Data management and analysis**

Data will be entered twice into a database using access software. The accuracy of data input will be checked and validated using a customized validation programme. The comparison of the incidence of malaria and severe malaria will be analysed using Poisson regression models. The statistical significance of differences in mean Hb will be assessed using t-test. We will consider the trials in the low and high transmission areas as separate and we recognise that trials is not adequately powered to make a direct comparison of the effects in the two areas.

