**Appendix 2**

**A comparative study of the efficacy of two or three doses of anti-malarial for IPTi in low transmission areas**

All IPTi studies currently under way utilise a schedule of drug administration which is very similar to that employed in the initial trial in Ifakara, Tanzania (13) with administration of the anti-malarial at the time of second DPT, third DPT and measles vaccinations, corresponding to the ages of approximately 3, 4 and 9 months. However, in low transmission areas relatively few infants will be infected with malaria before the age of about 6 months, in part because they are kept protected from exposure. In such situations, it is uncertain whether the schedule of drug administration for IPTi currently being advocated is appropriate; in such situations a two dose schedule with one dose given at the age of 4 months with DPT3 and the other at the age of 9 months with measles vaccine might be as effective as a three dose schedule, cheaper and safer.

For these reasons we propose a study in the South Pare district in which the efficacy of two and three dose regimens of the drug shown to be most effective in the present trial are compared. This would be an equivalence study with the incidence of clinical malaria during the first year of life and anaemia at the age of nine months as the main trial end-points. The study design would be similar to the one proposed in this submission and would use the same study team. However, until the first study has been completed, it is not known which would be the most appropriate drug to use for this study. Thus, investigation of this important issue has not been included in the present proposal, or budgeted for, but it is proposed as a potentially valuable continuation of investigations into the most effective ways of applying IPTi.

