**Assessment of Severity**

The most severe stage of the adverse reaction should be assigned to one of the following categories:

Mild: For example, an adverse experience which is easily tolerated by the subject, causing minimal discomfort not interfering with everyday activities, e.g. vomiting.

Moderate: For example, an adverse experience which is sufficiently discomforting to interfere with normal everyday activities e.g. headache.

Severe: For example, an adverse experience which prevents normal everyday activities e.g. necrotizing dermatitis (Stephen- Johnson syndrome).

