**Serious Adverse Events**

**Definition of Serious Adverse Events**

A serious adverse experience is any event which is fatal, life threatening, disabling or incapacitating or results in hospitalisation, prolongs a hospital stay or is associated with congenital abnormality, cancer or overdose (either accidental or intentional). In addition any experience which the investigator regards as serious or which would suggest any significant hazard, contraindication, side effect or precaution that may be associated with the use of the drug should be reported as a serious event.

**Life threatening** - An adverse experience is life threatening if the subject was at immediate risk of death from the event as it occurred; i.e. it does not include a reaction that if it had occurred in a more serious form might have caused death. For example, drug induced hepatitis that resolved without evidence of hepatic failure would not be considered life threatening even though drug induced hepatitis can be fatal.

**Disability/incapacitating**:- An adverse experience is incapacitating or disabling if the experience results in a substantial and/or permanent disruption of the subject's ability to carry out normal life functions.

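### The sentence that defines which adverse events go to the DSMB chair cites the wrong appendix and says *severe* where the protocol separately defines *serious*, leaving some non-fatal serious events with no stated route to the DSMB

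*Protocol*

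**What the plan says.** The reporting rules are in three places in the protocol.

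- **Section 4.8 (Monitoring compliance and safety), item 3.** The rule for the DSMB reads "Any severe adverse event, as defined in appendix 2, will be reported to the" DSMB chair. The time limit follows: "the chair of the DSMB within 1 week of the report being received". The next sentence concerns the company: "In addition, all serious adverse events will be reported to GSK regional office". Later in the section deaths get a rule of their own: "all deaths will be investigated by the post-mortem questionnaire technique and reported to the DSMB".
- **Section 5 (Monitoring of the trial).** "All serious adverse events will be reported to the local safety monitor by the project physician". This section mentions discussion with the DSMB where a drug-associated serious event leads the monitor to break a code or suspend the trial. It also says that the DSMB's requirements for adverse event reporting will be identified before the start and met, without saying what they are.
- **Appendices.** Appendix 2 is headed "A comparative study of the efficacy of two or three doses of anti-malarial for IPTi in low transmission areas". Appendix 3 holds the adverse event definitions and is marked as a draft still to be agreed with the DSMB. It grades intensity in one place: "Severe: For example, an adverse experience which prevents normal everyday activities". It defines the outcome-based class in another: "A serious adverse experience is any event which is fatal, life threatening, disabling or incapacitating or results in hospitalisation", followed by further criteria that include overdose.

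**The concern.** There are two defects in one operative sentence. The appendix it cites contains no definition of an adverse event, so it cannot be applied as written. Correcting the number does not settle the matter, because Appendix 3 defines *severe* and *serious* as different classes and the sentence uses the first. The company and the local safety monitor are to receive serious events, while the DSMB chair is to receive severe ones.

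At stake is whether the body asked to advise on safety is told of every event the protocol itself calls serious. Section 4.8 makes the safety and acceptability of mefloquine and Lapdap a major objective. Staff who follow the sentence literally could leave out a serious event that was not graded severe.

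**Working it through.** No arithmetic applies. The check sets the routing rules beside the definitions and asks, for each kind of event, who is told.

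**Step 1: the cross-reference.** The table of contents and the appendix itself agree that Appendix 2 is the proposal for a two- versus three-course study. It defines no adverse event. Appendix 3 does, so the definition of *severe* is misreferenced and not absent.

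**Step 2: the two classes.** The grade of *severe* turns on interference with everyday activity. The *serious* class turns on outcome: death, threat to life, disability, hospitalisation, overdose and others. Neither class contains the other.

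**Step 3: routes, with the appendix number corrected and the words read literally.**

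| Event | DSMB or its chair | Company | Local safety monitor |
|---|---|---|---|
| Death | Yes (own sentence, 4.8) | Yes | Yes |
| Non-fatal, serious, graded severe | Yes | Yes | Yes |
| Non-fatal, serious, graded mild or moderate | No stated route | Yes | Yes |
| Graded severe, not serious | Yes | No stated route | No stated route |

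**Step 4: whether the third row can be occupied under the protocol's own terms.** It can.

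- Overdose is serious by definition, whether or not symptoms follow. Section 4.7 has caretakers give the day 2 and day 3 doses at home. An accidental overdose without symptoms would be serious, with nothing to grade as severe.
- Appendix 3 gives vomiting as its example of a mild event, and hospitalisation makes an event serious. An admission for vomiting could meet the serious definition while the grading example points to mild.

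**Step 5: whether another provision covers the third row.**

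- The sentence on deaths covers deaths only.
- Section 4.7 (vomiting over the first three months) and section 4.8, item 1 (day-7 haemoglobin) send the DSMB specific data, not reports of serious events in general.
- Section 5 brings in the DSMB around code-breaking or suspension, not for every serious event.
- Appendix 3 requires all adverse events to be reported promptly to the trial coordinator and trial clinician, and states no onward step to the DSMB.
- The undertaking in section 5 to meet the DSMB's requirements states no rule.

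None of these sends a non-fatal serious event graded mild or moderate to the DSMB.

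**The case against.** The strongest reply is that this is a slip of the pen. The sentence on the company opens by saying that its reports are additional, which reads naturally as one class of event going to a second recipient. On that reading *severe* was meant as *serious*. The protocol also leaves DSMB reporting to be settled with the DSMB: section 5 promises to meet its requirements and to write standard operating procedures, and Appendix 3 is a draft for its agreement. Many infants admitted to hospital would probably be graded severe in any case.

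Much of this stands. A reader might infer that the protocol deliberately keeps serious events from the DSMB. The text does not support that, since a slip is at least as likely an explanation. But a probable intention is not a rule, and none of the provisions cited supplies one.

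Three further inferences should also be resisted.

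- **The DSMB's mefloquine and Lapdap reviews are compromised.** Vomiting and day-7 haemoglobin reach the DSMB by their own feeds, which this sentence does not touch. On both matters the DSMB recommends; it is not said to decide.
- **Event counts by arm will differ between recipients.** The rules describe reports of individual events, and none of these recipients is said to tabulate them by arm.
- **Replacing *severe* with *serious* is enough.** That would remove the present route to the DSMB chair for events graded severe that are not serious.

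**Conclusion.** The point holds as an internal inconsistency in a safety-reporting rule, and it is minor. The appendix number is wrong, and the word that triggers a report to the DSMB chair is not the one that triggers a report to the company and the local safety monitor. Read literally, the gap is non-fatal serious events graded mild or moderate.

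Its size cannot be worked out from the protocol, which gives no admission or overdose rate. It is probably small. The planned enrolment of 3,720 infants (1,280 + 2,440) is the population under observation and not the affected set. The deaths that section 4.8 anticipates, at least 100, fall outside the gap because they have their own route.

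The conclusion rests on two assumptions: that staff apply the sentence as worded, and that no agreement with the DSMB outside the protocol already sends it all serious events. If such an agreement exists, only the wording needs correcting.

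**What to change.** Reconcile section 4.8, section 5 and Appendix 3 by rewording the sentence in section 4.8 along these lines: *Any serious adverse event, as defined in Appendix 3, and any other event graded severe, will be reported to the chair of the DSMB*, with the present time limit kept.

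The DSMB then receives at least every serious event that the company and the local safety monitor receive, and loses none that it receives now. In terms of the table above, the third row gains a route to the DSMB and the fourth keeps the one it has.

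The cost is one sentence and a few more reports to the DSMB chair, already prepared for the other recipients. No dose, schedule or clinical rule changes.
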